### Sample size calculation

3.4

We estimated the sample size by the use of PASS 15. According to a previous study (Kim & Bang, 2018), the average time of achieving total enteral nutrition in the intervention group and control group is 28.3 days and 33.5 days respectively. This study is a superiority test of two independent means, desired power was set at 0.9, *α* was set at 0.025, *Zα* = 1.64, *Zβ* = 0.84. *σ* represents the standard deviation, and δ represents the difference between the mean values of each group. After calculation, 41 participants were needed for each group. Considering a 20% loss rate, 52 participants were needed for each group. A total of 104 participants should be included.

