### Statistical analysis

3.12

After the data for the entire sample has been collected, it will be performed using SPSS 25.0 software package. Missing data will be forecasted and filled using multiple imputations. A logistic regression model will be used to adjust for multiple potential confounders plain. Measurement data obeying the normal distribution will be expressed as mean (standard deviation), and t‐test will be used for comparing between two groups. Non‐normally distributed variables will be expressed as median (interquartile range), and compared by the use of non‐parametric Wilcoxon–Mann–Whitney test. Classification data will be described as cases count (construct Proportional) and compared using the chi‐square test or non‐parametric Wilcoxon–Mann–Whitney test. The confidence interval will be set at 95%. *p* < 0.05 will be considered statistically significant.

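### The printed z-values (1.64 and 0.84) belong to one-sided 5% and 80% power, not to the stated α of 0.025 and 90% power, and no SD is given to show which pair produced 41 per group

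*Protocol article*

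**What the plan says.** Section 3.4 of the protocol article (Sample size calculation) reports that the number was obtained with PASS 15. It describes the comparison thus: "This study is a superiority test of two independent means". From an earlier study it takes mean times to total enteral nutrition: "the intervention group and control group is 28.3 days and 33.5 days respectively". The error rates and their normal quantiles stand in one sentence: "desired power was set at 0.9, *α* was set at 0.025, *Zα* = 1.64, *Zβ* = 0.84". The symbols σ and δ are defined in words, but σ is given no value. The result is "After calculation, 41 participants were needed for each group", raised to 52 per group for 20% loss, or 104 in total.

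Section 3.12 (Statistical analysis) sets a 95% confidence interval and the criterion p "< 0.05 will be considered statistically significant". It does not say whether the test is one- or two-sided.

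**The concern.** Each quantile contradicts the error rate it should represent, and both are too small. Together they describe a recognisable but weaker design: one-sided 5% with 80% power. That makes a single slipped digit an unlikely explanation and raises the question of which design produced 41.

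This paragraph is the only justification for 104 infants on the primary outcome. If the weaker design was the one computed, the chance of missing the targeted 5.2-day difference at the usual two-sided 5% level is about 31%, not the 10% a reader would take from the text. A null result would then be read as stronger evidence against massage than it is. The Discussion adds to this risk by presenting the trial's sample size as large and criticising earlier studies for small ones.

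**Working it through.** **Inputs (section 3.4).** Means 28.3 and 33.5 days, so δ = 33.5 − 28.3 = 5.2 days. Stated α = 0.025 and power = 0.90. Printed Zα = 1.64 and Zβ = 0.84. n = 41 per group, 20% loss, 52 per group, 104 in total. The SD is not given.

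**Step 1: reproduce what can be reproduced.** The loss step holds: 41 / (1 − 0.20) = 51.25, rounded up to 52, and 2 × 52 = 104. The 41 cannot be reproduced without the SD.

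**Step 2: compare the quantiles with the error rates.**

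| Quantity | Value required | Printed | What the printed value means |
|---|---|---|---|
| α = 0.025 | 1.960 (one-sided) or 2.241 (two-sided) | 1.64 | one-sided α 0.0505, two-sided 0.101 |
| Power 0.90 | 1.282 | 0.84 | power 0.7995 |

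Neither reading of sidedness turns 0.025 into 1.64, and 90% power does not give 0.84. This step needs no assumption about the SD.

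**Step 3: size of the discrepancy.** With n = 2·[σ(Zα + Zβ)/δ]², n is proportional to (Zα + Zβ)² for a fixed SD.

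- Printed: (1.64 + 0.84)² = 2.48² = 6.15
- Stated (one-sided 0.025, 90%): (1.960 + 1.2816)² = 3.2415² = 10.51
- Ratio: 10.51 / 6.15 = 1.71

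**Step 4: solve for the SD that gives n = 41.** σ = δ·√(n/2) / (Zα + Zβ). Because 41 is a rounded-up figure, n between 40 and 41 gives a range.

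- Printed z-values: upper end 5.2 × √20.5 / 2.48 = 9.49 days, lower end 5.2 × √20 / 2.48 = 9.38 days.
- Stated α (one-sided) and power: upper end 5.2 × √20.5 / 3.2415 = 7.26 days, lower end 7.17 days. Using the noncentral t instead of the normal approximation gives 7.09 to 7.17.

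**Step 5: power at two-sided 5% (equal to one-sided 2.5%), noncentral t.**

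| Scenario | Implied SD | 41 per group | 52 per group |
|---|---|---|---|
| Printed z-values produced 41 | 9.49 | 68.8% | 79.0% |
| Stated α and power produced 41 | 7.26 | 89.3% | not at issue |

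In the first scenario, power at one-sided 5% with 41 per group is 79.2%, which is what 1.64 and 0.84 should deliver. The normal approximation gives 70% to 71% in place of 68.8% across SD 9.38 to 9.49, and the difference is only one of method. In the second scenario, 89.3% falls just short of 90% because 7.26 is the upper end of the normal-approximation range.

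Still in the first scenario, 90% power would take about 69 to 71 analysed per group by the normal approximation (87 to 89 after 20% loss). By the noncentral t at the upper end of the SD range it would take 72 (72 / 0.8 = 90).

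**Step 6: range over assumed SDs (41 per group, two-sided 5%).**

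| Assumed SD (days) | 7 | 8 | 9 | 10 |
|---|---|---|---|---|
| Power | 91% | 83% | 73% | 64% |

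**The case against.** The strongest reply is that no shortfall has been shown. The section says PASS 15 was used with α and power set at the stated values, and it never says that the printed quantiles entered the calculation. They may be textbook constants copied beside a correct software run. With an SD of about 7.1 to 7.2 days, 41 per group is what 90% power at one-sided 0.025 requires. Section 3.12 supports this reading to a degree: p below 0.05 beside a 95% interval is conventionally a two-sided 5% test, which matches α = 0.025 one-sided and not Zα = 1.64. The 69% and 79% also rest on a back-calculated SD that appears nowhere in the article, and on there being no superiority margin.

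Much of this stands. Underpowering is one of two scenarios, the power figures are illustrative, and a single requirement of 72 per group would be too precise. What does not stand is any defence of the sentence itself, because in either scenario it prints figures that are wrong. The convention in section 3.12 bears on Zα only and leaves Zβ and the SD open. Nor can the allowance to 52 be counted on as spare power: section 3.4 itself expects 20% loss, and section 3.11 drops infants who discontinue or deviate from the intervention.

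**Conclusion.** The concern holds. The stated α and power contradict the printed z-values in the same sentence. That finding is exact and does not depend on the SD. Worked as printed, the calculation delivers 80% power at one-sided 5%, not 90% at 0.025.

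The consequence for power depends on the unstated SD. At about 9.5 days (printed z-values used), power at two-sided 5% is about 69% with 41 analysed per group and 79% with 52. At about 7.2 days (stated α and power used), it is about 90% and the fault is confined to two misprinted constants. These figures assume a difference of 5.2 days, equal SDs, 1:1 allocation, no superiority margin and a t-test on means. The 90% claim cannot be relied on until the SD is given. The correction must be made because this paragraph alone supports the sample size.

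**What to change.** Rewrite section 3.4 from the inputs actually entered in PASS 15:

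1. Give the SD taken from the cited study.
2. State the primary test as two-sided at 0.05 (equivalent to one-sided 0.025), and say the same in section 3.12.
3. If the stated α and power produced 41, print Zα = 1.96 and Zβ = 1.28 and leave the numbers unchanged.
4. If 1.64 and 0.84 produced 41, keep 104 infants and restate the power, computed from the real SD, for 41 and for 52 analysed per group. At an SD of about 9.5 days these would be about 69% and 79%. They are illustrations and should not be copied in without the SD.

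The cost is one corrected paragraph and possibly a less favourable power statement. No added enrolment is needed to make the report accurate. If the sponsor wants to hold to 90% in the second case, the number would have to be recomputed. The article reports recruitment as still open, so the correction can be made before results are known.

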### Recruitment and informed consent

3.5

During the study period, all the neonates diagnosed with FI were evaluated to see if they fit our criteria. Researchers would introduce this trial to guardians of neonates who meet eligibility criteria in detail. Guardians acknowledged that data about their baby would be collected and used in research, they also acknowledged that they could choose not to participate in this trial and withdraw freely at any time, and this would not impact on their care. When guardians of the neonate agreed to participate in the trial, they were required to sign the informed consent. During the study period, the staff from the quality control department randomly selected the guardians of the subjects and asked them whether they understand the informed consent clearly, to ensure the rights and interests of the subjects and their guardians.

### Randomization and blinding

3.6

A third‐party personnel created a randomization schedule which was stratified by birth weight (1000–1499 g and 1500–2000 g) using a computer, and then provided it in sealed, opaque, consecutively numbered envelopes. Participants were assigned randomly to one of the two groups by opening the next envelope sequentially from the appropriate set. An independent research assistant responsible for randomization would inform the massager to perform massage when a neonate was assigned to the massage group, and he is the only person aware of which group the neonate had been assigned to. The massager also knows the list of massage groups. Both of them have no access to data of participants and are not responsible for statistical analysis. A researcher who has no access to the allocation group will perform all the assessments for our study.

### Variables studied

3.7

A researcher who has no access to the allocation group will perform all the assessments for our study. Table 2 shows the demographic variables including maternal characteristics and neonatal characteristics of participants recruited in our trial.

**TABLE 2 nop21733-tbl-0002:** Demographic variables.

Variables	Values
*Maternal characteristics*	
Caesarean delivery	Yes/no
Twin pregnancy	Yes/no
Gestational hypertension	Yes/no
Diabetes during pregnancy	Yes/no
Intrauterine distress	Yes/no
*Neonatal characteristics*	
Gestational age	Weeks
Day of recruitment	Day
Birth weight	g
Boy	Yes/no
Apgar score at 5 min	1–10
Weight at recruitment	g
neonatal critical illness score	Yes/no
Routine treatment received	Antibiotics/caffeine citrate/type of feeding

### Intervention

3.8

Intervention was provided by a massager (who has rich experience of neonatal nursing and has qualifications for neonatal massage). A 15‐min massage was performed on the massage group twice a day for 7 days. The massage began 30 min before feeding. Before the massage, the massager would thoroughly wash and disinfect hands and warm them. Neonates were placed in the supine position, and their heads and shoulders were pad 30°–45°. All the neonates were under ECG monitoring during massage.

The method of massage, frequency and application time were decided according to expert opinions found in previous studies (Diego et al., 2007; Heinonen et al., 2016; Kim & Bang, 2018; Tekgündüz et al., 2014; Zhu & Gong, 2021). And its biological plausibility and safety have been validated. Massage includes two parts: abdominal massage and skin stroking.

#### Abdominal massage

3.8.1

Starting from the infant's base of the ribs, run alternately with four fingers of your two hands vertically downward along both sides of the xiphoid process.Starting from the bottom of the ribs, beginning with the xiphoid, your left and right thumbs stroke simultaneously along the lower costal margin.Make the ‘I L U’ stroke: tracing ‘I’ down the infant's left costal margin. Then stroke across the infant's abdomen along the base of infant's right rib to his left rib and down, thus trace an inverted ‘L’. Then trace an inverted U. Stroke from the infant's right side, over and around the belly button, then under the left side.With the navel as the center of the circle, massage baby's abdomen clockwise.Start from the right side of the infant's abdomen, from top to bottom, and press the nine divisions of the abdomen gently.Hold the infants' legs with your hands, and make them bent. Then hold the baby's thigh close to the belly, and stay for 3–5 s.

#### Skin stroking

3.8.2

Tap 15 times or press gently on the sole of the foot.The forearm stroking: stroke baby's skin with your thumb or index finger from the elbow to the wrist stripes at the ulnar side of the forearm, each forearm needs 30‐s stroking. Then use your thumb or index fingers to stroke baby's skin from the wrist to the elbow stripes at the radial side of the forearm, about two 30 s each.

### Safety

3.9

As safety of massage has been proven in previous studies, our intervention would not induce any complications in most cases. And we took several measurements to avoid the occurrence of adverse events. The strength of massage was controlled so that the baby's skin changes just from pink to white. During massage, the massager paid close attention to the ECG monitor. Massage was suspended when the baby's vital signs (such as respiratory rate, heart rate and oxygen saturation) were not stable (Diego et al., 2009; Indrio et al., 2011), or the baby began to cry, urinate or defecate. Massager would continue massage only when the baby returns to a stable condition.

### Outcome

3.10

#### Primary outcome

3.10.1

The time (day) from initiation of enteral nutrition to total enteral nutrition, which is defined as a daily intake of ≥120 mL/Kg/day (Abdallah et al., 2013).

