## BACKGROUND

1

Over 14.9 million babies are born prematurely across the world every year, and the number is still increasing (Heinonen et al., 2016). Due to immature gastrointestinal function, premature newborns especially those born before 34 weeks, are susceptible to feeding intolerance (FI) (Asadi et al., 2019), and its morbidity could achieve 70% (Ng et al., 2019). Currently, there is no universal definition of FI, the widely accepted one is the following: the gastric residual volume (GRV) was 50% greater than the last feeding volume, with abdominal distension or vomiting (Moore & Wilson, 2011).

FI could badly influence newborns' health. During the neonatal period, it may lead to malnutrition, delayed enteral nutrition, prolonged hospitalization, growth restriction and increase the risk of sepsis and serious gastrointestinal complications such as necrotizing enterocolitis (NEC) (Meister et al., 2019; Neu, 2007). Additionally, it may lead to long‐term negative outcomes such as visceral obesity, glucose intolerance, and increased risk of cardiovascular disease, negative neurodevelopmental outcomes in adulthood (Asadi et al., 2019). At present, treatment for FI includes breastfeeding, modifications in feeding regimes, use of probiotics or medicine, but effectiveness and safety of these methods remain controversial (Basu & Smith, 2020; Fanaro, 2012; Sukwuttichai et al., 2021), feeding intolerance (FI) is still a thorny issue affecting the prognosis of preterm infants. So it is important to find an effective way to cure FI, contributing to recovery of gastrointestinal function and improving long‐term health of preterm infants.

In recent years, massage therapy has been frequently used in neonatal wards for the prevention of FI. Studies have shown that massage could prevent gastric retention and abdominal distention in premature infants, and reduce the length of stay. In addition, massage could stimulate the digestive system and the vagus nerve in premature infants, potentially improving their physical growth (Diego et al., 2007; Heinonen et al., 2016; Tekgündüz et al., 2014). However, there is no consensus on the efficacy of massage in the treatment of FI.

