### Participants: Inclusion/exclusion criteria

3.3

Table 1 specifies the criteria for inclusion, exclusion, termination and exit criteria. Inclusion and exclusion criteria were defined according to previous literature (Baldassarre et al., 2019; Ng et al., 2018; Yakobson et al., 2020).

**TABLE 1 nop21733-tbl-0001:** Inclusion, exclusion, termination and exit criteria.

*Inclusion criteria*
Meet the FI diagnostic criteria
Admitted to the Neonatal Treatment Center of the Affiliated Children's Hospital of Chongqing Medical University within 24 h after birth
28 weeks ≤ gestational age ≤ 34 weeks, 1000 g ≤ birth weight ≤ 2000 g
In clinically stable condition
The neonate's guardians are willing to participate in this trial
*Exclusion criteria*
Apgar score less than 4 at 5 min
Neonates with skin disease, intestinal obstruction, sepsis, necrotizing enterocolitis, gastrointestinal malformation, congenital heart disease, central nervous system disorder, immune deficiency, or any other disease that may affect the ability to eat and normal growth before recruitment
Neonates who need surgery which requires general anaesthesia (except for ligation of patent ductus arteriosus) before the day of randomization
Neonates whose blood pressure is not stable (using dopamine <5 mg /kg/min is permitted)
Ventilator dependent or FiO_2_ (Fraction of inspired oxygen) > 40% on the day of randomization (continuous positive airway pressure, nasal intubation, oxygen mask are allowed)
Neonates who are diagnosed with Grade III or IV ventricular haemorrhage (IVH) on the day or before randomization
*Termination criteria*
Discharge in a stable condition with doctor's advice
*Exit criteria*
Death or discharge before achieving total enteral nutrition
Guardian request to withdraw from the trail

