### Data collection and management

3.11

Table 3 shows the schedule of evaluations. Data of each participant were collected on case report forms (CRFs) and then electronically recorded on a computer. CRF1 records participants' baseline information and it was filled in when neonates were included in the trial. CFR2, which includes information about the outcome of this trial, will be filled in during the trial and when neonates discharge with advice.

**TABLE 3 nop21733-tbl-0003:** Schedule of evaluations.

	Staff member	CRF	T1	T2	T3	T4	T5	T6
Symptom of FI	Neonatal assistant	CRF1	**×**					
Informed consent	Research assistant	CRF1	**×**					
Contact information	Research assistant	CRF1	**×**					
Sex	Neonatal physician	CRF1		**×**				
Gestational age	Neonatal physician	CRF1		**×**	**×**			
Mode of delivery	Neonatal physician	CRF1		**×**				
Apgar score	Neonatal physician	CRF1		**×**				
Maternal issues	Neonatal physician	CRF1		**×**				
Weight	Neonatal nurse	CRF2		**×**	**×**			**×**
Gastric residual volume	Neonatal nurse	CRF2				**×**	**×**	
Abdominal circumference	Neonatal nurse	CRF2				**×**	**×**	
Frequency of defecation	Neonatal physician	CRF2				**×**	**×**	
Length	Neonatal nurse	CRF2		**×**				**×**
Head circumference	Neonatal nurse	CRF2		**×**				**×**
Time to achieving total enteral nutrition	Neonatal physician	CRF2						**×**
Duration of abdominal distension	Neonatal physician	CRF2						**×**
Duration of vomiting	Neonatal physician	CRF2						**×**

*Note*: T1, screening; T2, baseline evaluation; T3 randomization; T4, day 1 of intervention; T5, day 7 of intervention; T6, discharge.

Once recorded, data are locked to prevent changes. Access to the data is limited to researchers directly involved with this trial. Data about participants who discontinue or deviate from intervention will not be included in statistical analysis.

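### The primary outcome counts feeding days that precede randomisation, and the planned unadjusted comparison makes no allowance for them; this can cost precision but does not bias the result

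*Protocol article*

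**What the plan says.** Section 3.10.1 of the protocol article sets the primary outcome as "The time (day) from initiation of enteral nutrition to total enteral nutrition", with total enteral nutrition meaning a daily intake of at least 120 mL/kg.

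Entry comes later than the start of that clock. Table 1 lists "Meet the FI diagnostic criteria" as an inclusion criterion. Section 3.5 says that "all the neonates diagnosed with FI were evaluated to see if they fit our criteria", so diagnosis comes before screening. Table 1 does not restate the diagnostic criteria, but the Background gives the widely accepted definition: "the gastric residual volume (GRV) was 50% greater than the last feeding volume, with abdominal distension or vomiting". The footnote to Table 3 fixes the order of events: "T1, screening; T2, baseline evaluation; T3 randomization; T4, day 1 of intervention; T5, day 7 of intervention; T6, discharge". FI symptoms are recorded at T1.

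Table 2 collects "Day of recruitment" as a baseline characteristic. Section 3.6 stratifies randomisation by birth weight only. Section 3.12 compares groups by t-test or Wilcoxon–Mann–Whitney test; the only adjusted model it names is a logistic regression.

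**The concern.** A residual can be judged against the last feed only if feeding has begun. By the protocol's own sequence, first feed comes before diagnosis, diagnosis before randomisation, and randomisation before the first massage. The time from first feed to randomisation (the lead time below) is thus inside the primary outcome in both arms, although treatment cannot change it.

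If lead time differs between infants, it adds variation to the outcome. An analysis that ignores it leaves that variation in the error term, which widens the confidence interval and lowers power. The logistic model does not repair this, because it is unsuited to an outcome measured in days.

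There is also a smaller gap in the definition. No criterion in Table 1 requires that an infant has not yet reached 120 mL/kg/day, and section 3.10.1 does not say that the threshold must be reached after randomisation. Read literally, an infant who had reached it before FI appeared would have an outcome already settled at allocation.

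**Working it through.** **The plan's own figures.** Section 3.4 states that the mean time in the intervention group and "control group is 28.3 days and 33.5 days respectively", so δ = 33.5 − 28.3 = 5.2 days. The loss step reproduces: 41/0.8 = 51.25, rounded up to 52 per group, 104 in total. The 41 itself cannot be reproduced, because no SD is given. It can only be inverted, using n = 2[SD(Zα + Zβ)/δ]², so SD = δ√(n/2)/(Zα + Zβ):

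- Printed Z values: 5.2 × √20.5 / (1.64 + 0.84) = 9.49 days.
- Stated α of 0.025, taken as one-sided, and power 0.9: 5.2 × √20.5 / 3.242 = 7.26 days.

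The two differ because the printed Z values do not match the stated α and power. At 41 per group and two-sided 0.05, noncentral-t power is 68.8% with SD 9.49 and about 89% with SD 7.26. The 69% baseline therefore comes from that mismatch, not from the choice of clock.

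**Lead time independent of later time (assumption).** Let s be the SD of lead time, also assumed. Its share of the variance is s²/SD², and the SD left once it is accounted for is √(SD² − s²). With SD 9.49:

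| s (days) | Share of variance | Remaining SD | Power |
|---|---|---|---|
| 3 | 10% | 9.01 | 73% |
| 4 | 18% | 8.61 | 77% |
| 5 | 28% | 8.07 | 82% |

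With SD 7.26, the same steps take power from about 89% to 94%, 97% and 99%.

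**Lead time correlated with later time.** Let r be that correlation and q the SD of time from randomisation. Holding the total SD at 9.49, SD² = s² + q² + 2rsq, so q = −rs + √(SD² − s²(1 − r²)). Moving the clock to randomisation leaves SD q. Keeping the outcome and adjusting for lead time leaves residual SD q√(1 − r²). For s = 4 and r = −0.3, q = 1.2 + √(90.13 − 14.56) = 9.89, and the residual SD is 9.89 × √0.91 = 9.44.

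Power at 41 per group, for s = 3 / 4 / 5 (current analysis 69%; the adjusted column uses 78 degrees of freedom and credits no gain from the stratum):

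| r | Clock from randomisation | Outcome kept, adjusted |
|---|---|---|
| −0.4 | 62 / 61 / 62% | 69 / 69 / 69% |
| −0.3 | 65 / 65 / 67% | 69 / 69 / 71% |
| −0.2 | 68 / 69 / 72% | 69 / 71 / 74% |
| 0 | 73 / 77 / 82% | 73 / 77 / 82% |
| +0.2 | 79 / 84 / 90% | 80 / 86 / 91% |

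Moving the clock loses power once q exceeds SD, that is, when r < −s/(2·SD): below −0.16, −0.21 and −0.26 for s = 3, 4 and 5. Adjustment did not fall below the current analysis anywhere in this range.

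**The case against.** The strongest reply is that nothing here is invalid. Lead time is settled before allocation, so randomisation balances it in expectation, and an effect that is additive in days leaves the mean difference untouched. That stands, and it limits the point to precision.

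The size is also open to challenge. Neither the SD of 9.49 nor any lead-time SD appears in the article, and independence is an assumption. An infant enrolled later may already have advanced its feeds and need fewer further days, which would make r negative and shrink the gain or remove it. That also stands, and it is why moving the clock is not the preferred remedy. Section 3.4 does not say from which origin its planning means were counted, so a new origin could also separate the outcome from its sample-size basis.

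It may be said that day of recruitment is collected and that adjustment for confounders is planned. This helps only in part: the named model does not fit the outcome, and day of recruitment is not the same as days fed before randomisation.

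Four stronger readings are tempting, and the article does not support them:

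- **Immortal time.** This would concern a survival analysis, and section 3.12 plans none.
- **Chance imbalance as distortion.** A one-day difference in mean lead time would move the estimate by one day, or 1/5.2 = 19% of the planned effect. But that is ordinary sampling error, already within the standard error. For s of 3 to 5 and 41 per group, the standard error of that imbalance is s√(2/41) = 0.66 to 1.10 days.
- **Dilution of the effect.** This needs an effect proportional to post-randomisation time, which the article does not claim, and an origin for the planning means, which it does not give.
- **Outcomes actually settled before allocation.** Nothing shows that such infants are enrolled, and the exit criterion for death or discharge before full feeding presupposes that full feeding still lies ahead. Only the missing wording can be faulted.

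**Conclusion.** The point holds as one of efficiency. The primary outcome contains a pre-randomisation interval that massage cannot influence, and the planned comparison ignores it. The treatment estimate is not biased in expectation. The loss of precision cannot be calculated from the article. The illustrative rise from about 69% to 73–82% rests on the back-solved SD of 9.49, an assumed lead-time SD of 3 to 5 days, independence, 41 analysed per group and a two-sided 5% test. Under negative correlation the gain shrinks and can vanish. Of the two remedies compared, adjustment is the one to recommend, because under these assumptions it gives up nothing even where the gain is nil.

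**What to change.** - Keep the stated primary outcome. Make the primary analysis a linear model for days to full enteral nutrition, with treatment, birth-weight stratum (1000–1499 g or 1500–2000 g) and days of enteral feeding before randomisation as covariates.
- Add one sentence to section 3.10.1: the 120 mL/kg/day threshold must be reached after randomisation.
- Report time from randomisation to full enteral nutrition as a supplementary analysis.

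The cost is a wording change, recorded as an amendment before unblinding; section 3.14 reports recruitment as still open. The covariate needs only the date of first feed, which the outcome already requires, and the date of randomisation, a scheduled point in Table 3. Analysis costs two degrees of freedom, one for each covariate. Because the outcome is unchanged, any comparability with studies that count from first feed is kept.

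### Enteral intake and days fed at randomisation are not named as covariates for time to full enteral feeding, so the unadjusted primary comparison probably gives up precision

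*Protocol article*

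**What the plan says.** **Outcome.** Section 3.10.1 counts the primary outcome in days from the start of enteral feeding "to total enteral nutrition, which is defined as a daily intake of ≥120 mL/Kg/day". The clock starts at first feed, before randomisation.

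**Entry.** The first inclusion criterion in Table 1 is "Meet the FI diagnostic criteria". No criterion sets a range for enteral intake or for days of feeding at entry.

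**Baseline data.** Table 2 lists 13 variables. The nearest to feeding progress are "Day of recruitment", weight at recruitment, and a routine-treatment item coded "Antibiotics/caffeine citrate/type of feeding". Intake in mL/kg/day is not among them. Table 3 has no intake row at baseline (T2) or randomisation (T3); the row "Time to achieving total enteral nutrition" is completed only at discharge (T6).

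**Allocation and analysis.** Section 3.6 stratifies by birth weight only. In section 3.12 the t-test "will be used for comparing between two groups" if data are normal, and a Wilcoxon–Mann–Whitney test otherwise. The same section mentions a logistic regression to adjust for potential confounders, none of which is named.

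**The concern.** Two infants randomised on the same day of life may be at quite different points on the way to 120 mL/kg/day, and may have taken different numbers of days to get there. Both facts are settled before allocation and massage cannot change them. Together they describe how fast the infant was advancing and how much of the course remains, so both are plausibly prognostic for total days.

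An unadjusted test leaves that variation in the error term. With 41 to 52 infants per arm, a chance imbalance could also move the estimate, and the planned baseline table would not show it. Birth weight does not determine how far feeding had advanced when FI was diagnosed.

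The stated logistic model does not fill the gap, because it needs a binary outcome and the primary outcome is a number of days. At stake are the width of the confidence interval and power, not the validity of the test.

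**Working it through.** **1. The plan's own figures (section 3.4).** Means are 28.3 and 33.5 days, a difference of 5.2. The loss step reproduces: 41/0.8 = 51.25, so 52 per arm and 104 in total. The 41 cannot be reproduced because no SD is given. Solving n = 2[SD(zα + zβ)/5.2]² for n = 41 gives SD of about 7.2 with one-sided α 0.025 and power 0.90, or about 9.4 with the printed z values 1.64 and 0.84. (Those z values do not match the stated α and power, which is a separate matter.)

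**2. What adjustment is worth for a given R².** The residual SD is SD × √(1 − R²), and the standard error of the difference at 41 per arm is that × √(2/41). Power is at two-sided 0.05.

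| SD | R² | Standard error (days) | Power, 41 per arm |
|---|---|---|---|
| 7.2 | 0 | 1.59 | 0.905 |
| 7.2 | 0.25 | 1.38 | 0.965 |
| 9.4 | 0 | 2.08 | 0.707 |
| 9.4 | 0.25 | 1.80 | 0.824 |

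At R² = 0.04 the gain is slight: power is 0.916 and 0.725 respectively.

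**3. What R² might be (every input assumed).** For intake x at randomisation, total days = x/(rate before FI) + (120 − x)/(rate after FI).

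- Starting intake: uniform on 20–60 or 10–100 mL/kg/day.
- Mean rates before/after, as mL/kg/day gained per day: 10/5, 10/4, 15/4 or 8/6.
- Rates lognormal, with CV 20% or 40% and before–after correlation 0 or 0.5.

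That makes 32 scenarios, simulated with 200,000 infants each:

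| Covariates | R² range | Median |
|---|---|---|
| Intake alone | 0.005–0.64 | 0.13 |
| Days fed alone | 0.00–0.44 | 0.05 |
| Both | 0.08–0.71 | 0.41 |

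The reduction in standard error from using both is 1 − √(1 − R²): 4% at R² = 0.08, 23% at 0.41 and 46% at 0.71. For intake alone, R² is at most 0.21 when starting intake is 20–60, so its high values depend on the wider assumed spread.

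**4. Effect of a chance imbalance in intake.** The two spreads have SD 40/√12 = 11.5 and 90/√12 = 26.0. With 52 per arm, one standard error of the difference is SD × √(2/52) = 2.3 or 5.1 mL/kg/day. With the clock at first feed, one extra mL/kg/day of starting intake changes total days by 1/after − 1/before in size:

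- 8/6: 1/6 − 1/8 = 0.04
- 15/4: 1/4 − 1/15 = 0.18

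Using unrounded values, the extremes are 2.26 × 0.0417 = 0.09 days and 5.10 × 0.183 = 0.93 days, or 2% and 18% of 5.2.

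**The case against.** **Intake is not the outcome's baseline value.** A reader might take the outcome as distance still to go, and argue as follows: 120/33.5 = 3.58 mL/kg/day, so 5.2 × 3.58 = 18.6 mL/kg/day of starting intake is worth the whole target effect. The documents do not support this. The clock starts at first feed, so at constant pace total days = x/3.58 + (120 − x)/3.58 = 33.5 for every x, and the effect cancels. In expectation, intake alone matters only insofar as feeding advances at a different pace after FI than before. This objection stands in full, and no figure based on 3.58 is used here.

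**There is no bias.** Randomisation balances intake in expectation and the unadjusted test is valid. This also stands; anyone inferring a biased comparison would be wrong.

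**Adjustment is planned, and covariates may be named elsewhere.** Section 3.12 does announce adjustment, and a full protocol or SAP might list covariates, so it would be too strong to say that none will be used. But the article fixes the type of model, and that model does not fit days. Its data schedule also has no place for intake.

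**Much is already on file.** Day of recruitment is collected, admission is within 24 hours of birth, and the date of first feed and the feeding records are needed to derive the outcome. That is true. It makes the fix cheap, but day of recruitment is not days since first feed, and in the scenarios days fed alone explains little (median R² 0.05).

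**The magnitude is assumed.** No feeding rate or intake spread comes from the documents. The simulated mean durations are about 18–28 days, shorter than the plan's 28.3 and 33.5. The range runs from negligible to large and cannot be narrowed from the text.

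**Conclusion.** The point holds as a matter of efficiency and protection against chance imbalance. The article names no usable adjustment of the primary outcome for how far feeding had advanced at randomisation, and does not list intake as a baseline variable.

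The probable cost is precision. On the assumed rates and spreads, the standard error could be 4–46% lower with both covariates, and a one-standard-error imbalance in intake is worth about 0.1–0.9 days. The upper ends need a wide spread of starting intake and a marked slowing after FI. The direction is secure if these values are prognostic at all; the size is not established. The change is worth making because it is cheap, not because the planned test is invalid.

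**What to change.** - From the feeding records, take enteral intake (mL/kg/day) on the day before randomisation and days since first enteral feed. Add both to Table 2 and CRF1 and show them by arm.
- In section 3.12, replace the unadjusted test and the logistic model for the primary outcome with a prespecified linear model for days (or a time-to-event model), with treatment, birth-weight stratum and these two values as covariates. Fix the wording before the data are analysed by arm.

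The outcome definition can stay as it is. With days since first feed as a covariate, a linear model gives the same treatment estimate whether the response is total days or days remaining after randomisation.

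The cost is two CRF fields, retrievable for infants already enrolled if their feeding records are kept, plus a few degrees of freedom and a regression in place of a simple test. Allocation, treatment and sample size do not change.
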